### Outcomes

We will measure each indicator across the TB care cascade from TB screening to TB-free survival. (Table 2). Primary outcomes include the mean change in proportion of individuals (1) screened for TB disease, (2) initiated on TPT, or (3) initiated on TB disease treatment combined across all facilities during the intervention period (exposed) compared to baseline (unexposed). Primary outcomes were selected based on sensitivity to system-level improvements; they represent SAIA-TB steps that, if changed, would meaningfully alter patterns of TB-related morbidity and they are routinely collected. They are relatively easy to collect and readily understood by clinic managers and frontline staff. Indicators will be assessed monthly over the study period (including 12 months baseline, 18 months intervention, and 12 months maintenance phase).

**Table 2 Tab2:** SAIA-TB primary and secondary outcomes

SAIA-TB primary and secondary outcome variables	
**TB indicator (variable)**	**Numerator/denominator**
TB screening^a^	*#screened with WHO symptom screen* # target population
TB evaluation	*# receiving a diagnostic evaluation (GXP/LAM)* # positive screening
TB diagnosis	*# diagnosed with TB (GXP/LAM/clinical)* # who completed a diagnostic evaluation
Linkage to care for TPT^a^	*# initiating TPT* # negative diagnostic evaluation + eligible for TPT
Linkage to care for TB disease^a^	*# initiating TB treatment* # positive diagnostic evaluation
Successful TPT outcome	*# completing TPT* # initiating TPT
Successful TB outcome^b^	*# cure or complete treatment for TB disease* # initiating TB treatment
TB-free survival	*# TB-free (CXR/GXP) 12 months* *after initiating TPT or TB disease treatment* # successful outcomes for TPT or TB disease

*CXR* Chest x-ray, *GXP* GeneXpert, *LAM,* Urine lipoarabinomannan

^a^Primary outcome variable

^b^WHO definition

Secondary outcomes include the additional TB cascade indicators (TB evaluation, diagnosis, treatment outcome, and TB-free survival); however, some of these are more dependent on a mix of individual-level factors (i.e., adherence to medication) (Table 2). These indicators are clinically important and can be affected at a system-level. Outcomes will be assessed for all patients receiving care, as well as assessed by important sub-groups, such as by HIV status, age (under 5 years), and local municipality (cluster).

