### Exposure definition

Facilities will be considered unexposed prior to the initiation of the intervention in their local municipality and exposed thereafter. Individuals’ exposure to the intervention will be based on the exposure status of the facility in the calendar month in which they first entered TB care (including those newly identified as eligible for TPT and TB treatment and those already on TPT or TB treatment).

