### Data sources

Patient-level TB data will be sourced from existing programmatic Ministry of Health facility registries and patient-level forms. Slight modifications may need to be designed to capture the entire TB care cascade from screening to TB-free survival. Data will be abstracted from these existing paper registries and patient forms at least weekly by study personnel into a study database via REDCap on tablet or laptop [53]. As part of routine care, each patient with TB is assigned a unique identification number that links across service points and clinics, which will be used to abstract registry data for study outcome measures. The database will generate on-demand reports with monthly indicators to populate the TCAT.

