### Data analysis

Intervention analysis for primary outcomes will include generalized linear mixed modeling comparing study outcomes between exposed and unexposed times for outcomes described in Table 2 [31, 55]. Models will account for clustering by local municipality and will assess the impact of adjustment for patient-level covariates (i.e., age, sex, HIV status, and comorbidities) as well as clinic-level covariates (i.e., patient volume, staffing levels) and time (months since study initiation). We will assess missing data for randomness and employ multiple imputation, if possible [56, 57]. Additionally, we will assess outcomes among all individuals, including patients lost to follow-up, following an intent-to-treat principle [58–60]. Secondary analyses will test for interaction between exposure and time (temporal and time-to-exposure) to avoid a bias estimate of treatment effect [31]. We will also conduct a controlled, segmented time-series analysis incorporating monthly clinic-level estimates from the entire study period (segmented into 12-month baseline, 18-month intervention, and 12-month maintenance phases). This secondary analysis will allow us to fully use available data to assess intervention impact, address both serial and intra-class correlation, and assess temporal patterns in study outcomes [55, 58].

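### Neither primary initiation outcome has a time limit, so people eligible before the switch but started after it count as unexposed successes; this lowers the estimated effect, mainly for TPT

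*Protocol article*

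**What the plan says.** All references are to the protocol article.

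- **Outcomes, Table 2.** Two of the three primary outcomes are linkage proportions. For TPT the denominator is people with a "negative diagnostic evaluation + eligible for TPT"; for TB disease it is people with a "positive diagnostic evaluation". The numerators are simply those who start. No period for starting is given in either row. The only row with a time point is TB-free survival, at 12 months "after initiating TPT or TB disease treatment".
- **Exposure definition.** A person's exposure is "based on the exposure status of the facility in the calendar month in which they first entered TB care". The rule also covers "those already on TPT or TB treatment". The date of starting treatment plays no part.
- **Outcomes, text.** The primary contrast is worded by period: the intervention period against baseline.
- **Data analysis.** The mixed model compares exposed with unexposed time. A secondary segmented time series is described as "incorporating monthly clinic-level estimates from the entire study period".
- **Data sources.** "The database will generate on-demand reports with monthly indicators to populate the TCAT". Neither this section nor Data analysis says whether a start is dated to the month of initiation or to the month of eligibility.

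**The concern.** SAIA-TB shows staff where people drop out of the cascade and asks for rapid gains in the step they choose. Tracing people who were found eligible earlier but never started is a natural thing for a clinic to try. Under the entry-month rule, every such person who is then started raises the unexposed proportion. The programme's own success is credited to the comparator.

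Time available to start is also unequal. At the minimum phase lengths a facility is observed for 12 + 18 + 12 = 42 months. A person entering in the first baseline month has about 42 months in which to be counted as started; one entering in the last intervention month has about 12. If starts are counted only to the end of the intervention phase, the figures are 30 months and under one month. Both features favour the unexposed group.

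The article also points two ways on attribution. By entry month the late start belongs to baseline; by period it belongs to the intervention. With no window to limit late starts, the estimate for two primary outcomes depends on which section the analyst follows.

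**Working it through.** **Plan's own figures.** There is no power figure for the initiation outcomes to reproduce. The sample-size totals concern screening and are arithmetically right (978 x 5 = 4,890; 4,890 x 4 = 19,560). They play no part in this point.

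**Inputs**
- Baseline p0: 31% for TPT and 70% for TB treatment (Power and sample size). The unstarted shares are therefore 69% and 30%.
- Hypothesised gain: 20% for each outcome (Abstract, Methods). Relative or absolute is not stated, so both are shown. Relative gives p1 = 31 x 1.2 = 37.2% and 70 x 1.2 = 84%; absolute gives 51% and 90%.
- c: the share of eligible, unstarted baseline entrants who start after the switch. This is an assumption; 0% to 20% is shown.

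**Formulas (entry-month attribution, no time limit)**
- Unexposed proportion as finally counted = p0 + (1 - p0) x c
- Observed contrast = p1 - [p0 + (1 - p0) x c]
- c at which the contrast is zero = (p1 - p0) / (1 - p0)

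**Worked case, TPT, relative 20%, c = 10%:** 31 + 69 x 0.10 = 37.9%; 37.2 - 37.9 = -0.7 points, against a true gain of 6.2. The contrast is zero at 6.2 / 69 = 9.0%.

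| Outcome (reading of 20%) | p0 to p1 | True gain (c = 0) | c = 5% | c = 10% | c = 20% | Zero at c = |
|---|---|---|---|---|---|---|
| TPT (relative) | 31 to 37.2 | 6.2 | +2.75 | -0.7 | -7.6 | 9.0% |
| TPT (absolute) | 31 to 51 | 20 | +16.55 | +13.1 | +6.2 | 29.0% |
| TB treatment (relative) | 70 to 84 | 14 | +12.5 | +11.0 | +8.0 | 46.7% |
| TB treatment (absolute) | 70 to 90 | 20 | +18.5 | +17.0 | +14.0 | 66.7% |

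Contrasts are in percentage points. This is the plain exposed-minus-unexposed difference with one c for all baseline entrants. The planned mixed model adjusts for covariates and months since study start, so its estimate will not equal these figures exactly. That adjustment changes neither the person's exposure label nor the recorded outcome, so it does not remove the misattribution. The unequal time to start is not included in the table.

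**After the fix.** With one window from eligibility or positive result, starts after the window count for neither period. The target returns to 6.2 points (TPT) and 14 points (TB treatment) under the relative reading, apart from people whose window straddles the switch.

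**The case against.** **This is detail for the full protocol or analysis plan.** An initiation window and the dating rule of a secondary series are often left to a document not shown here, and they may be there. For the monthly series this stands: silence in the article is not an error. It does not dispose of the main point. The article itself states both the outcome definition and the exposure rule, and the misattribution follows from applying them together. The article also words the contrast in two ways that place the same start in different periods.

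**The backlog is assumed.** The 31% and 70% come from preliminary and national data, not from a list of people waiting at these clinics. Some non-starters will have declined, died, moved or ceased to be eligible. This stands: c has no basis in the documents and could be near zero.

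**Two stronger readings are not supported.**
- A reader might infer that the monthly series books the same start as an intervention success, so that the two analyses are pushed in opposite directions. The article never says how the series dates a start, nor whether a person evaluated again would join the later month's denominator. If the series groups people by eligibility month, it moves the same way as the individual model. The documents allow different attribution; they do not establish it.
- A reader might infer that both initiation outcomes could plausibly show no effect or harm. On the trial's own hypothesis TB treatment needs 46.7% of the unstarted group to be recovered before its gain disappears. A 5-point gain would vanish at 5 / 30 = 16.7%, but that difference is the one used to power screening, not the hypothesis for initiation.

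**Conclusion.** The concern holds in conditional form. As written, the primary initiation outcomes are open-ended and exposure is fixed at entry, so late starts under SAIA-TB raise the unexposed proportion and bias the individual-level effect toward the null, possibly past it. It is mainly a TPT problem: if the 20% is relative, a catch-up of 9.0% of unstarted baseline people erases the effect; if absolute, 29.0%. For TB treatment the bias is modest, leaving +11.0 of 14 points at 10% catch-up under the relative reading. These sizes rest on the assumed c, on a single c for all baseline entrants, and on the baseline rates quoted in the article. The direction under the Exposure definition does not depend on how the monthly series is built. Whether the series and the model disagree cannot be settled from the article.

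**What to change.** - In Table 2, define both linkage outcomes as started within one prespecified, fixed window from the date of eligibility (TPT) or of the positive result (TB treatment). Make it identical in baseline, intervention and maintenance, and short relative to the 3-month step.
- Attribute each person by month of eligibility or diagnosis in both the mixed model and the monthly series, and align the wording of Exposure definition, Outcomes and Data analysis with that rule.
- Score starts after the window as not linked in the primary proportion, and report them as a separate count by phase so that recovery of earlier non-starters remains visible.
- Settle the rule before outcomes are compared by exposure.

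**Cost.** Late starts no longer count in the primary proportion. People whose window straddles the switch remain mixed; a window short relative to the step keeps this group small. Two dates per person must be captured. Data sources describes patient-level abstraction at least weekly and allows form modifications, which makes this feasible, but the article does not confirm that the registers hold both dates. The linking number it describes is for patients with TB, so capture for TPT-eligible people without TB needs checking in particular.

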**Methods:**

This stepped-wedge cluster randomized trial will evaluate the effectiveness of SAIA on TB (SAIA-TB) cascade optimization for patients with TB and high-risk contacts across 16 clinics in four local municipalities in the Sarah Baartman district, Eastern Cape, South Africa. We hypothesize that SAIA-TB implementation will lead to a 20% increase in each of: TB screening, TB preventive treatment initiation, and TB disease treatment initiation during the 18-month intervention period. Focus group discussions and key informant interviews with clinic staff will also be conducted to determine drivers of implementation variability across clinics.

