Even less is known about the care cascade for TB prevention treatment (TPT) [25, 26]. An estimated 80% of South Africans are infected with TB [21, 27]. This has created a vast reservoir of people at risk of progressing to TB disease, especially recent contacts of TB patients and PLH [28, 29]. Therefore, it is imperative to screen and treat not only TB disease but also subclinical TB infection in this high burden setting [30]. This is critical as South Africa recently updated their TPT guidelines, expanding eligibility to all household contacts in late 2021 [31]. Understanding how guidelines can be optimized is critical to implementation success and sustainability [32]. A global meta-analysis of the TPT cascade from 2016 revealed that of individuals intended for TB screening, less than 19% successfully completed TPT, indicating an opportunity to leverage strategies to close gaps in TB care [25].

There is growing international recognition for interventions to end the TB epidemic; gaining political will, community acceptance, avoiding stigma, and emphasizing feasibility of eliminating TB are all critical [33, 34]. Passive case finding (PCF)—the notion of waiting until individuals become symptomatic with TB disease to report to the health system—is the most common form of case finding. However, this is insufficient to reduce TB incidence and prevalence. Rather, a systematic and comprehensive active case finding (ACF) strategy must be employed where programs search for and screen high-risk groups to detect disease at an earlier stage, ideally before further transmission [35]. Recently the WHO Asia–Pacific region published ACF optimization implementation lessons and evidence for achieving TB elimination, including 17 studies assessing community- and household-based TB programs focused on detection, prevention, and treatment [36]. These, along with other historical examples of TB elimination in Alaska, Greenland, and Australia, provide necessary examples of scalable implementation efforts [37–40].

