### Power and sample size

Power calculations are based on the primary outcome: mean change in proportion of individuals who complete screening for TB. TB screening was selected as the primary outcome as existing South African guidelines call for TB screening to be routinely implemented in outpatient services, and it is where the largest gap in the TB care cascade is currently. In a stepped wedge study, exposed and unexposed observation periods take the place of “arms” in parallel cluster trials. Outcomes (TB screening, TPT initiation, and TB treatment initiation) at baseline have been estimated to be 39% of eligible individuals screened for TB, 31% eligible individuals initiating TPT, and 70% eligible individuals initiating TB treatment per preliminary and national data (unexposed) [5, 23, 25]. We need a sample size of 978 individuals screened per cluster per time period to have 99% power (alpha = 0.05, and intracluster correlation of 0.01) to detect down to a 5% difference of proportion. Therefore, each cluster, over the course of all 5 time periods, needs to screen 4890 individuals. With four clusters, that will produce a total sample size of 19,560. Power calculations were completed using the Pass power analysis and sample size statistical software [54].

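### TB-free survival pools preventive-treatment completers with treated TB patients, so a change in their mix can move this secondary outcome when neither group's result has changed

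*Protocol article*

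**What the plan says.** In the Outcomes section, Table 2 lists the cascade indicators. Linkage to care has one row for TPT and one for TB disease, and so does successful outcome. TB-free survival has a single row. Its numerator counts people TB-free at 12 months "after initiating TPT or TB disease treatment", and its denominator counts "successful outcomes for TPT or TB disease". The text below the table makes it a secondary outcome.

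Two passages could have separated the groups again. The Outcomes section says that results will be assessed in sub-groups, "such as by HIV status, age (under 5 years), and local municipality (cluster". The Data analysis section says that models will assess adjustment for "patient-level covariates (i.e., age, sex, HIV status, and comorbidities", together with clinic-level covariates and time. Neither names treatment type (TPT or TB disease).

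On expected change, the Abstract hypothesises that "SAIA-TB implementation will lead to a 20% increase in each of: TB screening, TB preventive treatment initiation, and TB disease treatment initiation", without saying whether the 20% is relative or absolute. Power and sample size gives the baselines as "31% eligible individuals initiating TPT, and 70% eligible individuals initiating TB treatment".

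**The concern.** The two groups differ by construction. Under Table 2, the TPT row draws on people with a negative diagnostic evaluation, and the TB row on people with a positive one. There is no particular reason to expect both to have the same TB-free proportion 12 months after starting treatment.

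A pooled proportion depends on the two group proportions and on the share of each group in the denominator. The trial compares exposed with unexposed periods, and the intervention acts on the initiation steps that feed that denominator. Clinics choose which step to work on, and the cascade tool shows them the gain from optimising one step while the others stay the same (SAIA-TB implementation strategy, Step 1). Gains in TPT and TB treatment initiation may therefore be unequal.

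At stake is how the last step of the cascade is read. A rise or fall could reflect better results for TB patients, better results for TPT completers, or only a different proportion of each. An improvement in one group could also hide a deterioration in the other.

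**Working it through.** The documents state no figure for TB-free survival, so there is none to reproduce. The check asks how far the pooled indicator moves when the mix changes and both group proportions stay fixed.

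**Inputs from the protocol article**
- Baseline initiation: TPT 31%, TB treatment 70% (Power and sample size).
- Hypothesised rise: 20% in each (Abstract, Methods).
- Average household size: 3.42 (Study setting).

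**Assumptions, not in the documents**
- k, the number of TPT-eligible people per TB patient: from 1 to 2.42. The upper value is household size less the index patient, 3.42 − 1 = 2.42.
- The same probability of successful completion in both groups, so that completion cancels from the share.
- d, the difference between the groups' 12-month TB-free proportions: 5, 10 or 20 percentage points.

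**Formulas**
- TPT share of the denominator: w = k × p_TPT / (k × p_TPT + p_TB)
- Pooled indicator: w × (TPT proportion) + (1 − w) × (TB proportion)
- Change with both group proportions fixed: (w₁ − w₀) × d, towards the group whose share grows.

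**Baseline share**
- k = 1: 0.31 / (0.31 + 0.70) = 0.307
- k = 2.42: 0.7502 / (0.7502 + 0.70) = 0.517

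**Case A: 20% read as relative, in both.** Initiation becomes 37.2% and 84%. Both terms of the share are multiplied by 1.2, so w is unchanged for every k. For k = 1, 0.372 / (0.372 + 0.84) = 0.307. The shift is zero whatever d is, provided that the mix of eligible people stays fixed.

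**Case B: 20% read as percentage points, in both.** Initiation becomes 51% and 90%.
- k = 1: w = 0.51 / (0.51 + 0.90) = 0.362, a change of 0.055
- k = 2.42: w = 1.2342 / (1.2342 + 0.90) = 0.578, a change of 0.061

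| d (points) | Shift, k = 1 | Shift, k = 2.42 |
|---|---|---|
| 5 | 0.27 | 0.30 |
| 10 | 0.55 | 0.61 |
| 20 | 1.10 | 1.22 |

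**Case C: unequal gains, for illustration only.** TPT initiation rises by 20 points and TB treatment initiation does not change. The plan does not hypothesise this.
- k = 1: w = 0.51 / (0.51 + 0.70) = 0.421, a change of 0.115. The shift is 0.6 points for d = 5 and 2.3 points for d = 20.
- k = 2.42: w = 1.2342 / (1.2342 + 0.70) = 0.638, a change of 0.121. The shift is 0.6 and 2.4 points.

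**Cancellation.** At w = 0.517, suppose the TPT proportion rises by 2 points and the TB proportion falls by 2 points. The pooled indicator moves by 0.517 × 2 − 0.483 × 2 = 0.07 points, so it shows almost nothing.

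**Check on the fix.** Reported separately, each proportion moves by zero in cases A to C, because neither group's outcome has changed.

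**The case against.** A reader might infer that SAIA-TB sets out to change the TPT-to-TB mix. The documents do not say so. They hypothesise the same 20% rise in both initiation steps and state no aim about mix, and on the relative reading (case A) the shift is exactly zero. A change in mix is a possible by-product. This objection stands.

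A reader might also blame the guideline change, since the Background notes that "South Africa recently updated their TPT guidelines, expanding eligibility to all household contacts in late 2021". That expansion came before baseline work began in October 2023 (Study status), so wider eligibility applies in exposed and unexposed periods alike. Only continuing uptake could shift the mix between them. That would be a trend over time, and time is among the adjustments to be assessed. This stands too, although adjusting for calendar time would not remove a change in mix that the intervention itself produced.

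It would go too far to say that the trial could not separate the groups. The sub-group list is introduced as examples, the data are patient-level, and earlier rows already count TPT and TB disease separately. Nothing prevents a split.

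The article is condensed, and stratified reporting could be left to a fuller document. That answers a complaint about missing detail, but the point here is narrower. Table 2 fixes a definition, that definition pools, and no sub-group or covariate named in the article undoes it.

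Finally, the size depends on assumed values, and with equal group proportions there is no shift. That is correct. It limits the numerical claim but does not answer the problem of interpretation or of cancellation.

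**Conclusion.** The point holds as a cheap improvement to one secondary outcome. As defined, TB-free survival can move through case mix alone and can mask opposite changes in the two groups. Two conditions are needed for a spurious shift: the TPT share must differ between exposed and unexposed periods, and the groups must differ in their 12-month TB-free proportion. The documents establish neither, though both are plausible.

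Under a 20-point rise in each initiation step, the shift is about 0.3 to 1.2 points. This rests on 1 to 2.42 TPT-eligible people per TB patient, equal completion and a group difference of 5 to 20 points. The upper ratio counts household contacts only, whereas people living with HIV are also a priority group, so the true ratio may lie outside this range. Unequal gains could give a larger shift. The shift is zero under an equal relative rise with a fixed eligible mix.

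A reader might infer that the trial's main result is at risk. It is not: the three primary outcomes and the power calculation do not use this indicator.

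**What to change.** Split the TB-free survival row of Table 2 in two, as the table already does at linkage and at successful outcome:
- TB-free at 12 months among TPT completers;
- TB-free at 12 months among people successfully treated for TB disease.

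Analyse and report each separately. If one combined figure is wanted, show it only as a supplement, standardised to the baseline TPT:TB mix.

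The cost is one extra table row, one extra model and less precision in each group than in the pooled estimate. The two denominators are the numerators of the existing successful-outcome rows. The numerator needs each 12-month result to be tied to the treatment received. The Data sources section describes a linking identification number for patients with TB and does not say the same for TPT recipients, so the team should confirm that treatment type is carried through to the 12-month record.
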